### 3.5. Maintenance

The sustainability of the changes will be assessed by measuring the parameters at the baseline, after the six months intervention, and at the end of the study (Table 1).

### 3.6. Statistical Analysis

The continuous distributions will be described using means with standard deviations; regarding categorical data, the number of cases with percentages will be used. Differences between the intervention group and the control group will be tested using an independent samples *t*-test, a Pearson Chi-Square test, or a Fisher’s Exact test. Regression analyses will be used to evaluate the role of physical activity in the changes to physical fitness and the number of sick leave days. Changes in physical fitness and the number of days of sick leave, according to follow-up times and for comparison of the study groups, will be analyzed using general/generalized linear models (univariate, multivariate, and repeated measures) and regression analyses. The drop-out rate can be determined by comparing the number of participants attending baseline measurements to the number of participants attending follow-up measurements. Intention-to-treat analysis will be used to compare changes induced by the implemented intervention of the treatment groups, including all participants as originally allocated after randomization. In addition, a per-protocol analysis will be used to compare changes in the intervention participants who completed the treatment originally allocated. P-values under 0.05 are considered statistically significant. IBM SPSS Statistics version 26.0 for Windows (SPSS Inc., Chicago, IL, USA) was used for statistical analyses.

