### 2.5. Measurements

All participants will be subject to baseline measurements at the beginning of the study, and similar measurements at the end of the study. Following the intervention, the intervention group participants will again be subject to all these measurements to observe the effects of the intervention. The control group participants will be subject to physical activity measurements via an RM42 accelerometer for two weeks, to examine whether any changes in their physical activities have taken place due to participation in the study, even without taking part in the intervention.

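### Some models named for change over follow-up need complete visits, which does not fit the promised intention-to-treat set and would leave no controls in a three-visit fitness analysis

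*Protocol article*

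**What the plan says.** **Analysis set.** Section 3.6 commits to intention-to-treat, "including all participants as originally allocated after randomization". It separately plans "a per-protocol analysis will be used to compare changes in the intervention participants who completed the treatment originally allocated".

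**Models.** For fitness and sick leave over follow-up, and for comparing the groups, section 3.6 names "general/generalized linear models (univariate, multivariate, and repeated measures", together with regression, run in "IBM SPSS Statistics version 26.0 for Windows". It does not say which of these carries the group comparison or which visits enter it.

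**Drop-out.** It is to be counted ("The drop-out rate can be determined by comparing the number of participants attending baseline measurements"). The article assumes no rate.

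**Visit schedule.** Section 2.5 says that after the intervention "the intervention group participants will again be subject to all these measurements". For controls at that time it says "The control group participants will be subject to physical activity measurements via an RM42 accelerometer for two weeks". Table 1 agrees: at the end of the intervention the control column is marked for the RM42 accelerometer and is empty for questionnaire, body composition, fitness and laboratory tests. Both arms have every measurement at baseline and at the final visit, six months later.

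**Outcomes.** Section 3.1 makes fitness change a primary outcome. Section 3.5 judges maintenance from all three time points.

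**The concern.** A multivariate or repeated-measures general linear model takes one row per person and deletes any row with a missing visit. That sits badly with a promise to analyse everyone allocated. Here the schedule itself creates missing visits: no control can have a fitness value at the end of the intervention.

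Two things are at stake. First, an analyst who fits one of these named models to fitness at three visits is left with one arm. Second, one who falls back on change from baseline to the final visit has both arms but only the attenders, and sets aside the intervention arm's end-of-intervention values, which could help correct for selective loss. Selective loss is plausible because the trial cannot be blinded and only the intervention arm wears the interactive device, keeps a diary and receives counselling.

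**Working it through.** **1. Which visits carry which primary outcome (Table 1, sections 2.5 and 3.1)**

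| Outcome | Baseline | End of intervention | Final visit |
|---|---|---|---|
| Fitness, intervention | yes | yes | yes |
| Fitness, control | yes | **no** | yes |
| Accelerometer, both arms | yes | yes | yes |
| Sick-leave days | counted over calendar periods, not tied to a test visit | | |

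A complete three-visit fitness row is impossible for a control. This needs no assumption about drop-out.

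**2. Numbers kept, as an illustration**

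Section 2.3 gives 175 soldiers + 99 civilians = 274 for fitness. Section 2.2 gives 2:1 allocation: 274 × 2/3 ≈ 183 intervention, leaving 91 controls. Let p be the proportion missing at each follow-up visit; the values of p are assumed.

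- Three visits, intervention: 183 × (1 − p)² if absences are independent, 183 × (1 − p) if the same people miss both follow-ups.
- Three visits, control: 0.
- Two visits (baseline and final): 183 × (1 − p) and 91 × (1 − p).

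| p | 3 visits, intervention (independent / same people) | 3 visits, control | 2 visits, intervention | 2 visits, control |
|---|---|---|---|---|
| 0% | 183 / 183 | 0 | 183 | 91 |
| 10% | 148 / 165 | 0 | 165 | 82 |
| 20% | 117 / 146 | 0 | 146 | 73 |
| 30% | 90 / 128 | 0 | 128 | 64 |

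**3. Can a model using all available visits recover the contrast?**

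A simulation of 60 runs used 183/91 people, a true effect of 0.30 SD, correlation 0.8, no control value at the middle visit, and intervention drop-out depending on baseline. Listwise deletion over three visits kept on average 133 intervention participants and 0 controls. A mixed model and generalised estimating equations (GEE) each kept all 183 + 91 and returned 0.297 and 0.300 at the final visit.

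**4. How far a two-visit change analysis can go wrong**

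Assumptions, none from the article: true final effect 0.20 SD; correlations 0.8, 0.8 and 0.7; logit of missing the last visit = −1.5 − k × (observed change to the end of the intervention) in the intervention arm, and −1.5 in controls, which is 1/(1 + e^1.5) ≈ 18%. Two independent sets of runs (3,000 and 4,000) gave:

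| k | Two-visit change | All observed visits |
|---|---|---|
| 0 (loss unrelated to response) | 0.195 and 0.201 | 0.196 and 0.201 |
| 1 | 0.252 and 0.248 | 0.204 and 0.199 |
| 2 | 0.289 and 0.290 | 0.198 and 0.199 |

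Relative error is about 0.05/0.20 = 25% at k = 1 and 0.09/0.20 = 45% at k = 2. At k = 2 the figure moves between about 0.28 and 0.31 with the end-of-intervention effect assumed. With the sign reversed (k = −1) the two-visit estimate is about 0.13 to 0.15, an understatement. The standard error is about 0.11, so the k = 1 bias is roughly half a standard error.

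**The case against.** The strongest reply is that section 3.6 names a family of models, not one. The word generalized covers GEE, which does not need complete rows, and univariate and regression models are named too. A two-visit fitness comparison keeps controls who attend. No passage says that fitness will be compared between arms across three visits in a single model. The choice of model and the handling of missing values may sit in an analysis plan that is not shown, and the empty control cells are a matter of schedule, not of drop-out.

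Most of this stands. A reader might infer that the trial's estimate will be a completer estimate, or that controls vanish from its comparisons. The documents do not support either. The first depends on which named model is used. The second is confined to three-visit analyses of fitness and of the other measures controls miss at that visit. It does not apply to accelerometer activity and need not apply to sick-leave days. Section 3.2 defines the secondary outcomes from baseline to the final visit, when both arms are measured.

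What the reply does not remove is that the article does fix something: an analysis set, a list of models and a schedule. Two of the listed models cannot deliver that set for a primary outcome under that schedule. GEE is not a full answer either, because ordinary unweighted GEE generally relies on values missing completely at random.

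**Conclusion.** The point holds in a limited form. The general linear model options in section 3.6 that need complete visits do not fit the stated intention-to-treat set. For fitness at three visits they would keep 0 controls at any drop-out rate, so the group-by-time effect could not be estimated. That conclusion rests only on Table 1, section 2.5 and how these models treat incomplete rows.

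The size of any bias in a two-visit analysis is not known. A reader might take 25% to 45% as the expected overstatement. That range belongs to one assumed mechanism, in which intervention participants who do not improve leave more often. It disappears when loss is unrelated to response and changes sign when the dependence is reversed. The recovery of 0.20 by the all-visits estimate likewise assumes that loss depends only on observed values.

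The abstract adds to the problem. It says both arms are measured at all three times and then lists the measurements without exception. For controls at the end of the intervention this is true of the accelerometer only. The change is worth making because it touches a primary outcome and costs very little.

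**What to change.** - In section 3.6, replace the repeated-measures general linear model for continuous repeated outcomes with a linear mixed model: arm by visit, baseline included, all available visits, and everyone randomised who has any value.
- For fitness, state that the arm contrast is taken at the final visit, the only follow-up at which both arms are tested. The control cell at the end of the intervention is empty, so no arm contrast should be promised there. The intervention arm's values at that visit still enter the model.
- Reconcile the abstract with Table 1 on what controls undergo at the end of the intervention.
- Optionally, add a sensitivity analysis that penalises missing intervention values.

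The cost is wording. The named SPSS version offers mixed models, and no new data are needed.

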## 3. Results

### 3.1. Primary Outcomes

The primary outcome variables will include changes in accelerometer-measured physical activity, physical fitness test results, and days of sick leave absences. Changes in physical activity levels will be evaluated by comparing physical activity measurements at the baseline and after the intervention. Changes in fitness test results will be evaluated by fitness tests results (i.e., changes in maximal aerobic capacity, SLJ distance, and number of sit-ups and push-ups). Changes in sick leave absences will be evaluated by comparing the number of days of sick leave absences in the year prior to the intervention with the number of days of sick leave absences during the intervention, and with the number of days of sick leave absences one year after the intervention. In addition, each participant’s mean daily number of steps, increases in mean daily total time, increases in number of light physical activities and moderate-to-vigorous physical activities, and reductions in mean daily total time of sedentary behavior will be assessed via two weeks of accelerometer recordings of physical activity at the baseline, immediately after intervention, and six months after intervention.

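### Nine or ten unranked primary variables, each judged at p < 0.05, give roughly a 25–40% chance of at least one false primary finding if the intervention has no effect

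*Protocol article*

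**What the plan says.** Section 3.1 (Primary Outcomes) opens with three domains: "The primary outcome variables will include changes in accelerometer-measured physical activity, physical fitness test results, and days of sick leave absences". It then lists variables within them.

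- **Fitness:** four results, namely "changes in maximal aerobic capacity, SLJ distance, and number of sit-ups and push-ups".
- **Accelerometer:** "mean daily number of steps, increases in mean daily total time, increases in number of light physical activities and moderate-to-vigorous physical activities", and sedentary time, where "reductions in mean daily total time of sedentary behavior will be assessed via two weeks of accelerometer recordings". The times are "at the baseline, immediately after intervention, and six months after intervention", so there are two post-baseline assessments.
- **Sick leave:** the preceding year is the reference for two windows: "number of days of sick leave absences during the intervention, and with the number of days of sick leave absences one year after" its end.

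Section 3.6 (Statistical Analysis) says that changes in fitness and sick leave "will be analyzed using general/generalized linear models (univariate, multivariate, and repeated measures) and regression analyses". It adds intention-to-treat and per-protocol analyses, and closes with the threshold "P-values under 0.05 are considered statistically significant".

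No section ranks a variable, time point or window first, splits alpha, sets a testing order, or requires that several outcomes succeed together.

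**The concern.** The article fixes both the set of primary variables and the threshold applied to them. Taken together, they allow about ten separate chances of a significant primary result at the 5% level, before repeated time points and alternative models are counted. With no statement of what would make the trial positive, a report could lead with whichever variable crossed 0.05 and still be consistent with the protocol.

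The Discussion says that promising results could lead to the technology being applied in the general working population. It does not define promising, so the evidence behind that step could be one chance finding.

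**Working it through.** **Inputs.** The per-test level is 0.05 (Section 3.6). Sidedness is not stated, and two-sided tests are assumed. The counts come from Section 3.1:

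| Domain | Variables |
|---|---|
| Fitness | 4 |
| Accelerometer | 5 (steps, total time, light activity, moderate-to-vigorous activity, sedentary time), or 4 if total time is read as part of the light and moderate-to-vigorous items |
| Sick leave | 1 variable, 2 windows |
| Total, one test per variable | 9 or 10; 11 with both sick-leave windows and five accelerometer measures |

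The documents give no family-wise error rate to reproduce and no correlations between outcomes. The correlations below are assumptions.

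**Independent tests, no effect on any outcome:** error = 1 − 0.95^k.

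- k = 9: 1 − 0.95^9 = 37.0%
- k = 10: 1 − 0.95^10 = 40.1%
- k = 11: 1 − 0.95^11 = 43.1%

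**Ten equally correlated two-sided normal test statistics** (numerical integration over the shared component):

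| Pairwise correlation | Chance of at least one p < 0.05 |
|---|---|
| 0.3 | 35.1% |
| 0.4 | 32.1% |
| 0.5 | 28.7% |
| 0.6 | 25.1% |

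**Correlation within domains only** (5 + 4 + 1 variables, domains independent): 1 minus the product of the three domains' chances of no rejection.

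| Within-domain correlation | Chance of at least one p < 0.05 |
|---|---|
| 0.3 | 37.9% |
| 0.5 | 34.5% |
| 0.7 | 29.6% |
| 0.8 | 26.6% |

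**Narrower reading of Section 3.1.** The detailed accelerometer list comes in a final sentence framed as an addition. If those items are not primary, what remains is one overall activity measure, four fitness results and sick leave, six in all: 1 − 0.95^6 = 26.5% if independent. Counting both sick-leave windows gives 1 − 0.95^7 = 30.2%.

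**More than one test per variable.** The second follow-up, the alternative models and the per-protocol analysis are not counted above and would raise the figures. As a marker, 20 independent tests would give 1 − 0.95^20 = 64.2%.

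**After the fix.** Three tests, one per domain, each left at 0.05 would give 1 − 0.95^3 = 14.3% if independent. At 0.05/3 = 0.0167 each, the figure is 1 − (1 − 0.0167)^3 = 4.9%. Holm keeps it at or below 5% under any correlation.

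**The case against.** **An analysis plan may hold the adjustment.** This is a condensed article, and alpha allocation and test order are often left to such a plan. The 0.05 sentence is also generic and compatible with adjusted p-values. That is fair as far as it goes, and the absence of adjustment details alone would not be a finding. But the article itself names the primary set and states one threshold for it, so a later hierarchy would have to qualify what is written here.

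**The hypothesis is a conjunction.** The Introduction expects improvement in activity, fitness and sick leave together. If all had to succeed, the error rate would not be inflated. No section makes joint success the criterion, however. The opposite reading also goes too far: a reader might infer that the plan counts any one hit as trial success, but no section says so. The article has no success rule of either kind.

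**Ten separate tests are not fixed.** Multivariate and repeated-measures models can test several outcomes or times jointly. They are listed beside univariate models, and none is made a gate for the individual tests.

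**Single measures already exist in two domains.** Section 2.3 bases the sample size on one fitness index and on sick leave of seven or fewer days. This stands, and it helps the fix. Section 3.1 does not carry those quantities over: it splits fitness into four results and counts sick-leave days without that limit.

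**The size depends on assumptions.** This also stands. Accelerometer measures from the same recordings could be strongly correlated, and the count of ten is one reading. A reader might take 30–40% as the firm figure, but the documents do not support that lower limit.

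**Conclusion.** The concern holds. Followed as written, Sections 3.1 and 3.6 allow a chance of at least one false primary finding of roughly 25–40%, against a nominal 5%. The upper end is ten independent tests. The lower end is pairwise correlation of about 0.6, or the narrower count of six independent variables (26.5%).

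The range assumes no effect on any outcome, two-sided tests and one test per variable. Correlation stronger than assumed would lower it, and further time points, windows or models would raise it.

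The weakness is an undefined primary claim. It does not show that the trial will be declared positive on one result, or that any wider use is tied to a p-value. It should be corrected before outcomes are compared between arms.

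**What to change.** Name one between-arm comparison and one time point per domain:

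- **Fitness:** the fitness index of Section 2.3, at the visit six months after the end of the intervention. By Table 1 this is the only follow-up at which both arms take the fitness tests.
- **Sick leave:** short sick leave as used in Section 2.3, in one stated window.
- **Physical activity:** one accelerometer measure at one follow-up, chosen by the investigators before any outcome is compared between arms. Table 1 records both arms at both follow-ups.

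Test the three with Holm at a family-wise 0.05, so that the ordered p-values are compared with 0.0167, 0.025 and 0.05. Report all other variables, times and windows as secondary, with confidence intervals. Alternatively, keep the full list as primary and apply Holm across it. With ten tests the smallest p-value must then be below 0.05/10 = 0.005.

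No new data are needed, but this changes the definition of the primary outcomes and costs power. The article gives no power, so as an illustration assume 80% at two-sided 0.05. At 0.0167 the critical value rises from 1.960 to 2.394, and power falls to Φ(1.960 + 0.842 − 2.394) = Φ(0.408) ≈ 66%. Holding 80% would take (2.394 + 0.842)² / (1.960 + 0.842)² ≈ 1.33 times the sample. From 90%, power falls to Φ(1.960 + 1.282 − 2.394) ≈ 80%. This is the cost for an outcome that must pass the strictest Holm step; later steps cost less. The Section 2.3 sample sizes (about 175 soldiers and 99 civilians for fitness, 115 and 97 for sick leave) should therefore be checked, and their power restated, at the adjusted level.

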## 4. Discussion

This article provides an overview of the protocol and evaluation of health and physical training in a study by the Finnish Defence Forces. It is hypothesized that our intervention will increase the physical activity of the study’s participants, leading to reduced sick leave absences, improved fitness test results, reduced stress levels, improved values of the studied health-related biomarkers, reduced waistline circumference and body fat, decreased body mass, and improved reported lifestyle habits. The improved physical activity and health status will increase the readiness of military personnel for response crisis management and other operations, as well as the performance of their daily tasks in the workplace. In addition, an intervention using smartphone application technology to improve physical activity is cost-effective. If promising results are gained among military workers from the intervention, then accelerometer smartphone application feedback technology, combined with feedback from a physical education specialist, could be applied in the general working population to improve exercise habits on a larger scale.

## Figures and Tables

**Figure 1 mps-05-00001-f001:**
[figure not shown]
Participants in the different phases of the study.

**Table 1 mps-05-00001-t001:** Intervention procedure and measurements of the study.

	Intervention Group	Control Group
Baseline measurements before the intervention		
Questionnaire	X	X
Body composition measurements	X	X
RM42-Accelerometer measurements	X	X
Fitness tests	X	X
Laboratory tests	X	X
Intervention lasting six months		
Movesense accelerometer measurements and smartphone application feedback	X	
Telephone counselling	X	
Measurements after the intervention		
Questionnaire	X	
Body composition measurements	X	
RM42 accelerometer measurements	X	X
Fitness tests	X	
Laboratory tests	X	
Measurements after six months from the end of the intervention		
Questionnaire	X	X
Body composition measurements	X	X
RM42 accelerometer measurements	X	X
Fitness tests	X	X
Laboratory tests	X	X

## Data Availability

The data presented in this study are available on request from the corresponding author. The data are not publicly available due to the research permit policy of the data owner.
